## Abstract

**Background:** Adverse childhood experiences (ACE) can have negative effects on cognitive, social and emotion regulation abilities, which can threaten the child’s school integration and capacity to learn. While steady relations to sensitive, understanding adults may moderate these negative outcomes, the difficulties of children with ACEs pose a major challenge for teachers, whose insufficient preparation may lead to career attrition.

**Objective:** Psychoeducational trauma-informed care (TIC) interventions targeting teachers may strengthen teacher preparation and buffer the deleterious outcomes of ACEs, yet the evidence-base for these interventions is limited. Importantly, while minority groups are overrepresented among those with ACEs and additionally risk exposure to ethno-racial trauma, TIC interventions lack a social disadvantage/discrimination perspective. The Present trial addresses these issues.

**Method:** The study protocol employs a quasi-experimental design for assessing effects of a psychoeducational TIC intervention carried out in Swedish schools by Save the Children, Sweden (SCS). We compare, for the first time, an intervention group (*N* = 160) and a control group (*N* = 160) over time (pre-intervention, immediately after, 6 and 12 months post-intervention), assessing teacher stress, compassion fatigue, self-efficacy and trauma-informed knowledge. We monitor teacher attitudes and attributions of students’ academic weaknesses and behavioural and mental difficulties. The trial is preregistered (DOI:10.17605/OSF.IO/V7SH8).

**Results:** We hope that the mitigating effects of the SCS-TIC school intervention may be independent of social category, and that the trial will additionally generate knowledge of how providers and recipients of TIC may respond to it differently depending on their social and cultural identities. As school-based TIC practices and interventions are expansively relied on as means of preventing teacher burnout and career attrition, and buffering negative consequences of ACEs for children, establishing their effects with methodological robustness is important and timely.

**Conclusion:** Such knowledge may be used to tailor and target interventions to specific populations, while ensuring maximum effectiveness.

## Background

1.

Adversities during childhood have profound and far-reaching consequences for the child’s development and well-being, constituting a significant risk of mental illness, unemployment, poverty, and criminality in adulthood (Bellis et al., 2019; Davidson et al., 2010). Among the prevalent forms of adversity focused on in the seminal Adverse Childhood Experiences (ACEs) study (Felitti et al., 1998) were child abuse (physical, emotional and sexual), child neglect (physical and emotional), and dysfunctional parental caregiving (domestic violence, substance abuse, mental illness, criminal activity or parental absence). Other common forms of childhood adversity include loss of loved ones, poverty, peer rejection, dramatic and frequent relocations, bullying, racism, and discrimination (Bernard et al., 2021). Notwithstanding individual differences, it is not unusual that ACEs cause traumatic stress reactions with lasting detrimental effects on overall functioning (Felitti et al., 1998; Oral et al., 2015). Thus, ACEs can be considered as potentially traumatic, but whether they result in trauma or not depends on several interacting factors (Bartlett & Sacks, 2019).

Crucially, ACEs have a negative impact on cognitive and social abilities, such as attention, executive functioning, decision making, self-regulation, social competence, and communication skills, all of which are decisive for the child’s academic engagement and development (Shonkoff et al., 2012; Steiner et al., 2016; Stokes, 2022; Van der Feltz-Cornelis et al., 2019). As research has demonstrated, it is 2.5 times more likely for individuals who report four or more ACEs to suffer impairments crucial for their education (e.g. difficulties in self-regulating abilities and high levels of perceived stress) (Anda et al., 2006), leading to low achievement, absence problems, risky behaviours, suspension, and early drop out or expulsion (Bellis et al., 2018; Cook et al., 2005; Delaney-Black et al., 2002; Ford et al., 2006; Porche et al., 2016). However, research demonstrates that caring, attentive parents and other important adults, such as teachers, can play a crucial role in protecting children from the deleterious consequences of early childhood adversities, serving to mitigate the risks on further development (Van der Kolk, 2005; Verschueren & Koomen, 2012).

In fact, quality in the child – teacher relationship at preschool predicts academic and behavioural outcomes at school age (Broberg et al., 2012). Conversely, in the absence of attentive and supportive significant adults, ACEs may lead children to perceive adults as potential threats, impeding their ability to form healthy relationships, and students with ACEs are more prone to encountering conflicts with school staff and teachers (Fazel et al., 2014). The ecology of human development model (Bronfenbrenner & Morris, 2006) highlights this intricate and interconnected interplay between multiple contexts in the child’s growing environment and describes how alterations in any one system might influence child development in several ways. Thus, children with ACEs are in the forefront of risk for strained and conflictual relationships to teachers and other adults in the school setting, which may exacerbate and amplify the negative outcomes of their ACEs.

Difficult student behaviour presents a significant challenge for teachers, evidenced by the substantial number of teachers who cite the difficulty of handling students with behavioural challenges as the primary reason for leaving the profession within four years (Greene, 2008). Thus, many teachers may feel unprepared when faced with challenging child behaviours. Importantly, teachers who themselves have ACEs are at risk of re-traumatisation, as interactions with traumatised children may bring their own traumatic memories and difficult emotions forward, and lead to burnout (Fazel et al., 2014). Indeed, there is evidence that a quarter of new teachers will leave the profession within one year, possibly highlighting the toxic stress from unpreparedness in handling increasing numbers of children with difficulties, and, for some, simultaneous secondary traumatisation (Aloe et al., 2014). Perceptions of being poorly equipped to cope with student challenging and disruptive classroom behaviours, and lack of access to support systems within the school, is another highlighted reason for this pattern of career attrition among teachers (Fazel et al., 2014). Research suggests that conflictual teacher-student relationships might in part stem from miscommunication rooted in limited understanding of the impact of ACEs on learning abilities (Di Lemma et al., 2019). Thus, the urgent need of addressing teachers’ knowledge and understanding of how ACEs and trauma affect children in the educational environment is pivotal in efforts to limit the consequences of trauma.

### Psychoeducational trauma-informed care intervention in the school setting

1.1.

Since having at least one significant relationship characterised by trust and security increases child resilience (Masten, 2014), interventions aimed at the teacher–child relationship may buffer behavioural problems and poorer school performance later on, potentially contributing to the children’s long-term resilience. Psychoeducational trauma-informed care (TIC) interventions directed to teachers and other school personnel is such support. While referred to as trauma-informed care, TIC interventions encompass the entire range of challenges associated with ACEs and trauma. TIC interventions vary widely but the overall aim is to promote safety and resilience in children who have been exposed to adversities, whereas the psychoeducational TIC interventions directed at caregivers focus on increasing caregivers’ recognition, knowledge, and awareness of childhood trauma (Middleton et al., 2019; SAMHSA, 2014).

Psychoeducational TIC interventions directed at teachers and other school personnel are increasingly used internationally (Avery et al., 2021), and studies indicate decreased levels of secondary traumatic stress and burnout (Sprang & Garcia, 2022), increased trauma-informed attitudes among school personnel, including among teachers with positive trauma-informed attitudes pre-training (MacLochlainn et al., 2022), and a strengthened proactive and supportive classroom environment (Stokes, 2022) post-intervention. One TIC intervention directed at teachers and school personnel is based on the *Three pillars of transforming care* model (Bath, 2015). By providing teachers with knowledge about trauma, the programme hopes to help them understand and meet the needs of children and adolescents who have experienced trauma (Bath & Seita, 2019). TIC programmes based on the Three pillars model in out-of-home care result in higher levels of caregiver efficacy and decreased child behavioural difficulties (Lotty et al., 2020; Purvis et al., 2015). However, besides an unpublished pilot with a pedagogical perspective (Herbert et al., 2017), the Three pillars interventions in the school setting have not been evaluated.

### Social discrimination and childhood adversity

1.2.

While there is appreciation of, and promise in, TIC interventions, a notable limitation stems from insufficient consideration of how social categories and social group memberships interact and shape children’s experiences of ACEs, including collective experiences of trauma (Ginwright, 2018; Middleton et al., 2019). Intersectionality, a term coined by critical race theorist Kimberlé Crenshaw in the late 80’s to capture the unique experience of violence against black women, highlights the compounding effects in how social identities intersect and shape our unique experiences. Crenshaw (1989) argued that violence against black women could not be fully grasped if examined through the lens of either racism or sexism, but rather through considering racism and sexism conjointly.

Arguably, then, the comprehensive understanding and effective action for buffering long-term effects of ACEs on children requires consideration of the intricate intersections of social identities and segments of socio-economic strata. These intersections shape and govern our daily lives, and influence both our unique experiences of adversity and those of resilience. For instance, research suggests that racism is so ubiquitous in the lives of black youth that, independent of the presence or absence of other ACEs, they encounter an average of five instances of racial discrimination per day (English et al., 2020), constituting a major source of stress in the lives of members of ethnic and racial minority groups (Bernard et al., 2021). Consistently, research has emphasised that the profound and compounding deleterious effects of everyday experiences of racial discrimination may be best understood through the perspective of trauma and traumatic stress (Saleem et al., 2020). Incorporating knowledge about racism, discrimination and minority group-related experiences within an extended, culturally-informed framework of ACEs and TIC is thus essential (Bernard et al., 2021).

### Childhood adversity and school-based trauma-informed care intervention in Sweden

1.3.

Experiences of adversities in childhood are common also in a Swedish context. Among Swedish youth, 15% reported experiences of some form of negative exposure in childhood, and 10% reported two or more types of negative exposure before the age of 12 (Hagborg et al., 2018). In response to the Swedish government’s assignment (U2019/03787/S) to support the quality of education for newly arrived, non-Swedish-speaking children, and acknowledging the need for enhanced trauma knowledge among educational staff (Skolverket, 2023), Save the Children Sweden (SCS) was commissioned by the Swedish National Agency of Education in 2017 to train school personnel in a psychoeducational TIC school programme based on the Three Pillars intervention. Notably, among the conditions of the Swedish National Agency of Education for enrolling schools to the programme are that the school (a) has newly arrived children and children with immigrant background, and (b) is located in a socially vulnerable area.

Evidently, experiences of racism and racial discrimination are relevant in the Swedish setting. Statistics Sweden reports substantial disparities between children with a foreign background and those with a native Swedish background across various crucial aspects of life, including socio-economic status, family dynamics and educational opportunities (SCB, 2020). For example, more than 40% of children (0–17 years) with foreign (i.e. immigrant) background live in areas burdened by socio-economic challenges, compared to 5% of children with Swedish background. A recent report by SCS (Rosenlundh et al., 2021) indicates that every second child has witnessed racism in the school setting, and every fourth child reported to have experienced discrimination and/or harassment. A fifth of all children reported being afraid of being bullied because of their ethnic background. Notably, the children perceived adults as passive, seldom intervening or doing anything to stop racism in school (Rosenlundh et al., 2021). The school environment appears to be a primary setting where racism against children is perpetrated (Rosenlundh et al., 2021). Thus, an ethnic and culturally informed ACEs framework is highly warranted.

### Aims and objectives of the planned study

1.4.

Despite paucity of empirical evidence of the effectiveness of TIC interventions, clinical research data indicate that an increased knowledge among caregivers concerning trauma and TIC practices leads to changed TIC attitudes (Brown et al., 2012). A recent meta-analysis of TIC interventions within the child welfare system indicated that caregivers reported reduced child PTSD symptoms and behavioural problems but only moderate improvement on children’s wellbeing (Zhang et al., 2021). However, while recent international studies regarding trauma-focused interventions are encouraging (Angelöw et al., 2023; Izzo et al., 2016; Purvis et al., 2015), most evaluations of TIC interventions suffer from methodological shortcomings and lack robust methods such as a control group or longer-term follow ups (Fondren et al., 2020; Hanson & Lang, 2016). In a school setting, the Three pillars intervention directed at teachers (Bath et al., 2021) has never been evaluated.

Therefore, the purpose of this study is to assess the effect of psychoeducational interventions in trauma-informed care directed at teachers. Building on the limited existing empirical evidence (MacLochlainn et al., 2022; Zhang et al., 2021) we expect that, after training in TIC, participants will report changed attitudes toward trauma-informed care and related practices (H1). These effects will be associated with increased perceived teacher efficacy, classroom management strategies (H2). Moreover, we expect decreased reported burnout and compassion fatigue symptoms (H3). Finally, we expect that these effects will be present also 6-months post-training (H4). Due to the underexplored nature of psychoeducational TIC interventions in terms of interactions with awareness about ethno-racial trauma and community specific experiences of ACEs, we refrain from making predictions concerning how the intervention might influence awareness about such socioeconomic and intersectional aspects of ACEs and trauma.

## Methods and design

2.

### The trauma informed care (TIC) psychoeducational intervention for schools

2.1.

The SCS psychoeducational TIC school programme (Bath et al., 2021) provides a pedagogical framework for understanding how significant adults create conditions for healing and recovery in children who are exposed to trauma. With an aim of developing teachers’ ability to respond to pupils with a trauma-informed approach, the 5-day programme builds around the themes of safety, connections, and coping (Bath, 2015), and provides education about compassion fatigue and secondary traumatic stress, practical TIC training, and workshops on TIC implementation at an organisational level. TIC-ambassadors continue to work closely with the principal and support the TIC organisational implementation after finished training. For participation in the SCS-TIC programme, school principals must apply to the Swedish National Agency for Education, who then, based on the school’s written application and interviews with the school principal, select (prioritise) based on parameters including implementation capacity and the likely prevalence of trauma in the pupil population.

### Study design

2.2.

We employ a quasi-experimental design with four measurements: Pre-training baseline (T1), directly after termination of training (T2), six months (T3) and twelve months (T4) after baseline. An experimental group (training in SCS TIC-programme) will be compared to a control group (no training in SCS TIC-programme). Participants in the control group will receive the same questionnaires with the same time interval between the measurement occasions.

### Participants and recruitment

2.3.

Participants will be teachers and other professionals in the school context (principals, special teachers, school nurses) working in Swedish schools, from primary school to high school. Participants in the experimental group (*N* = 160) will be recruited from schools who participate in the SCS-TIC training programme. Sixteen (16) training groups consisting of 35 people each participate in the SCS-TIC training programme each semester. Participants will be excluded if they do not complete the programme. An equally large control group (*N* = 160) will be recruited from schools not receiving the SCS-TIC programme. For recruitment, participants in the experimental group will be contacted through collaboration with SCS. Participants in the control group will be invited to the study through e-mail and targeted on social media platforms.

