### Data collection

2.4.

For data collection, we use a digital platform that sends invitations to participation and unique personalised links via email/SMS, allowing participants to respond in their own time, via smartphone, tablet or computer. Data is safely and reliably combined by the digital platform software, without personal codes or human handling, thereby maximising confidentiality and minimising risk of error. It will be possible for participants to listen to the survey questions and information about the study.

Given that the experimental group is determined by the standardised procedure of the Swedish National Agency for Education who handles the applications for participation in the SCS-TIC programme, it cannot be claimed that the experimental group is randomly selected. Nevertheless, although access to school (socioeconomic and ethnic) data is restricted by current state regulations, we strive to match the schools that contribute to the experimental group with schools of similar student population composition (class sizes, proportion of immigrant students), geographic location (i.e. urban or suburban-located schools), and socioeconomic status (i.e. location of the school) in the control group. Schools in the control group are randomly selected among those who match on the above criteria, based on a draw.

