### Power/sample size calculations, data analysis plan and attrition analyses

2.7.

A power analysis employing R and G*Power with an aimed .80 power, significance level of .05 and an effect size of *d* = .5, yielded a sufficient sample size of *N* = 99 for our basic analyses. Estimating a drop-rate of about 40% over time, perhaps even higher for the control group, we determined a target sample size of *N* = 160 for the experimental group and *N* = 160 for the control group.

Data from all measures will be analysed using R (R Core Team, 2021) and JAMOVI (The Jamovi Project, 2022). Attrition analyses will be conducted, and missing data among participants who have completed all four measurements will be handled either utilising multiple imputation or by applying maximum likelihood estimation when employing the mixed linear model analysis. Independent *t*-tests will assess potential differences between experiment and control group concerning outcome measurements (e.g. perceived teacher efficacy, classroom management strategies, burnout and compassion fatigue symptoms) at baseline. For hypothesis testing, we will employ mixed linear model analyses of repeated measures to estimate fixed (i.e. the trauma-informed care training) and random (e.g. participants’ social class, gender, ethnicity) effects of training on the study outcome variables, comparing both within individuals (repeated measures analysis) and between groups (experimental versus control group measures at each timepoint). Interaction factors in the models are used for estimating potential moderation by ethnicity, socioeconomic status and other characteristics. For example, a three-way interaction of gender, ethnicity and social-class may uncover intersectional outcomes particularly for women with non-Swedish backgrounds that might indicate a heightened trauma-informed care approach to vulnerable students independently of whether they are in the experimental or control group.

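### Programme non-completers are excluded after enrolment, which can happen only in the experimental group; this weakens comparability with controls and may inflate the estimated effect

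*Protocol article*

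**What the plan says.** Section 2.3 (Participants and recruitment) sets the rule: "Participants will be excluded if they do not complete the programme". It does not define completion and names no counterpart for controls.

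Section 2.2 (Study design) places T1 before training and T2 directly after it. Controls get no training: "Participants in the control group will receive the same questionnaires with the same time interval between the measurement occasions". Section 2.3 adds: "An equally large control group (*N* = 160) will be recruited from schools not receiving the SCS-TIC programme". Control staff enter by their own response: "Participants in the control group will be invited to the study through e-mail and targeted on social media platforms". Section 2.4 (Data collection) describes matching of schools and then: "Schools in the control group are randomly selected among those who match on the above criteria, based on a draw".

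Section 2.7 says "Attrition analyses will be conducted", without detail. It describes missing-value handling (multiple imputation or maximum likelihood) only for people who answered on all four occasions, in either group. It plans baseline t-tests, then mixed models that compare both within individuals and between groups at each time point. It mentions no analysis that keeps staff who left the programme. The limitations in section 3 cover attrition, the untreated control group and the lack of randomisation, but not this exclusion.

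**The concern.** The rule selects on an event that occurs after baseline and can occur in one group only. If the tendency to finish a five-day training is related to how a person's scores would develop anyway, dropping non-completers creates a group difference that the training did not cause. The protocol gives reasons to expect a relation. Its background section says teachers with adverse experiences of their own risk re-traumatisation and burnout, its ethics section says attendees may leave the room before disturbing material, and burnout and compassion fatigue are among the outcomes.

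The rule also narrows the question. The estimate describes people who finished, whereas a school or agency deciding on the programme needs the effect in the staff who are enrolled. Every hypothesis test uses the population this sentence defines. If excluded staff are no longer surveyed, their later data cannot be recovered.

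**Working it through.** **The plan's own figures.** None bears on programme completion. The sample size of 99 (d = 0.5, power 0.80, alpha 0.05) is matched as a one-sided total over two groups: 4 × ((1.645 + 0.842)/0.5)² = 98.92, rounded up to 99. The text states neither reading, and the figure neither supports nor weakens this point. The target of 160 per group with 40% dropout leaves 160 × 0.6 = 96 per group.

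**Step 1: where the rule acts.** T1 precedes training, and completion is known only at its end, so the exclusion is post-baseline. Controls have nothing to complete, so it can act only on the experimental group. An attrition analysis can describe who was lost but does not return them to the comparison.

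**Step 2: shift with no true effect.** Assumptions, not in the document: a share q does not complete, and a normally distributed tendency to complete has correlation rho with outcome change. The completers' mean then shifts by rho × φ(z_q)/(1 − q), in SD units. The false-positive risk is two-sided at a nominal 0.05, with 160 × (1 − q) × 0.6 experimental and 96 control participants.

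| q | φ(z_q)/(1 − q) | rho = 0.1 | rho = 0.3 | rho = 0.5 | false-positive risk at rho = 0.3 |
|---|---|---|---|---|---|
| 5% | 0.109 | 0.011 | 0.033 | 0.054 | 0.056 |
| 10% | 0.195 | 0.019 | 0.058 | 0.097 | 0.068 |
| 20% | 0.350 | 0.035 | 0.105 | 0.175 | 0.105 |
| 30% | 0.497 | 0.050 | 0.149 | 0.248 | 0.155 |
| 40% | 0.644 | 0.064 | 0.193 | 0.322 | 0.212 |

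The range is about +0.01 to +0.32 SD. At rho = 0 the shift is zero. At rho = −0.3 the sizes are the same as at +0.3 with a negative sign.

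**Step 3: selection on baseline level only.** Suppose completion depends only on the T1 score (correlation rho), and T1 and follow-up correlate r. With k = φ(z_q)/(1 − q), completers shift by rho × k at T1 and by r × rho × k at follow-up, so the change contrast shifts by −(1 − r) × rho × k. With r = 0.6 and rho = 0.3 (assumed):
- q = 20%: −0.4 × 0.3 × 0.350 = −0.04 SD
- q = 30%: −0.4 × 0.3 × 0.497 = −0.06 SD

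The follow-up level contrast moves the other way: 0.6 × 0.3 × 0.350 = +0.06 and 0.6 × 0.3 × 0.497 = +0.09 SD. Direction therefore depends on what completion is related to and which contrast is read.

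**Step 4: effect among all enrolled staff.** If completers gain 0.5 and non-completers gain nothing, the effect is 0.5 × (1 − q): 0.40 at q = 20% and 0.35 at q = 30%. With 96 per group, two-sided power is about 0.79 and 0.68, against 0.93 at d = 0.5.

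**The case against.** The strongest objection concerns direction. A reader might infer that the estimate is biased upward. The document does not establish that, because it gives neither a completion rate nor reasons for leaving. If leavers simply start out more stressed, a stable difference in level cancels from a group-by-time contrast, and regression to the mean can turn the shift slightly downward (step 3). Upward bias in change requires completion to be related to prospective change. This stands, and it limits what can be claimed. It does not remove the problem, because section 2.7 also compares groups at each time point, where a level shift counts.

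A reader might also infer that completers are set against unselected controls. That is too strong. Control schools are matched and drawn, control staff are volunteers, and the protocol expects about 40% dropout, perhaps more among controls. Selective loss of controls could add to or offset the shift. Controls are unselected only with respect to programme completion.

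Third, the hypotheses are worded as effects following training, so a completers question is not plainly at odds with the stated purpose. That is fair: the defect is the missing all-enrolled comparison, not a contradiction.

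Two further defences fail. Lack of randomisation is no excuse, since the school selection is outside the investigators' control but this extra selection step is their own. Nor is the matter merely left to an unseen analysis plan, because the exclusion is stated outright.

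**Conclusion.** The point holds as a matter of design: a post-baseline exclusion that can act in one group only makes the groups less comparable and may inflate the effect. Nothing stated in section 2.7 undoes it.

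Size and sign remain open. Every shift in the table rests on assumed non-completion and an assumed correlation with outcome change. At the low end it is negligible, and at the high end (0.32 SD) it is more than half of the planned d = 0.5. Which case applies can be learned only if non-completers stay under observation, and the present rule does not provide for that.

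**What to change.** Replace the sentence in section 2.3 with: *All staff with a T1 measurement in a programme school stay in the experimental group, are sent T2–T4 on the same schedule as their training group whether or not they finish the training, and are analysed in that group.* Tying T2 to the training group's schedule settles when it falls for someone who leaves early.

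In section 2.7, fit the likelihood-based mixed model to all participants with a T1 measurement in both groups, without requiring all four measurements. Otherwise staff kept by the new sentence could drop out again through the missing-data rule.

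Record days attended (0–5), define completion, report the number of non-completers and their reasons, and give the completers-only result as a labelled sensitivity analysis.

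The cost is two changed sentences, one attendance variable and a few more invitations through the existing digital platform. The estimate and power may be lower, as step 4 shows. The investigators keep their completers analysis alongside a main analysis that no longer selects on programme completion.

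### The control group is labelled untrained, but the recruitment rule asks only that the school is not receiving the programme, and no step screens, records or handles training among controls before T4

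*Protocol article*

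**What the plan says.** Two sentences in the Protocol article define the control condition. Study design describes "a control group (no training in SCS TIC-programme)". Participants and recruitment says that controls are "recruited from schools not receiving the SCS-TIC programme". The first describes people or a group, the second describes schools, and neither gives a period.

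On the programme, section 1.3 says that the provider "was commissioned by the Swedish National Agency of Education in 2017 to train school personnel". Participants and recruitment adds: "Sixteen (16) training groups consisting of 35 people each participate in the SCS-TIC training programme each semester". Section 1.3 lists among the enrolment conditions that the school "has newly arrived children and children with immigrant background, and (b) is located in a socially vulnerable area".

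Control schools are to be matched to "schools of similar student population composition (class sizes, proportion of immigrant students)" and also on geographic and socioeconomic location, and then drawn at random from the matches (Data collection). On how individuals are approached: "Participants in the control group will be invited to the study through e-mail and targeted on social media platforms".

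Follow-up runs to T3 and T4, at six and twelve months after baseline (Study design). Background variables does not list earlier training in this programme. The limitations in the Discussion name the absence of a control intervention, response bias, attrition and non-randomisation, but not exposure of controls.

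**The concern.** The matching is sensible against confounding, but it has a side effect. Immigrant share and school location are close to the programme's own enrolment conditions, so the control draw is concentrated on schools that the programme may already have served or may admit next. Under the recruitment sentence alone, a school trained in an earlier semester is no longer receiving the programme and could be drawn. According to section 2.1, such a school may still be implementing the approach through its ambassadors. Nothing in the article says how a control school admitted between T1 and T4 would be treated.

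At stake is the interpretation of a small or null difference at follow-up. Without a record of exposure, a real loss of effect could not be told apart from controls having had the same training. The information cannot be recovered reliably once the survey waves have closed.

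**Working it through.** **Inputs.** Power .80, significance level .05, d = .5, N = 99, dropout about 40% and 160 per group (section 2.7). Intake is 16 groups of 35 per semester (section 2.3). T3 and T4 fall at 6 and 12 months after baseline (section 2.2). The share of controls exposed is not given and is assumed below.

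**The plan's own figure.** The total for a two-group comparison by normal approximation is 4 × ((z for alpha + z for power)/d)².
- One-sided .05: 98.9, so 99 reproduces as a total.
- Two-sided .05: 125.6, or 63 per group.
- Read as 99 per group, which the 160-per-group target suggests, power would be about 94% two-sided.

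The present point does not depend on which reading was meant. After 40% dropout, 160 × 0.6 = 96 per group remain, and that number is used below.

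**Intake during follow-up.** 16 × 35 = 560 people per semester. Assuming two semesters a year, a 12-month follow-up spans about two intakes. The first is roughly the one that supplies the experimental group, and its schools are not eligible as controls. That leaves about one later intake, 560 people, before T4, and less opportunity before T3. The number of eligible schools or staff is not given, so this count cannot be turned into an exposed share.

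**Direction of the bias by timing.** Let a be the share of controls trained before T1 with a stable, full effect, and b the share trained between T1 and the wave in question, also with full effect.
- Baseline difference (experimental minus control): −a × d
- Between-group difference at the wave: d × (1 − a − b)
- Difference in change from baseline: d × (1 − b)

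With d = .5:

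| Case | Baseline difference | Difference at the wave | Difference in change |
|---|---|---|---|
| a = 20%, b = 0 | −.10 | .40 | .50 |
| a = 0, b = 20% | 0 | .40 | .40 |

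Training during follow-up therefore dilutes both kinds of comparison. Stable earlier training dilutes the comparison at each timepoint and shifts the baseline, but cancels in the change from baseline.

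**Size, for between-group contrasts only.** Let c = a + b, with diluted effect .5 × (1 − c). Power is from the noncentral t, two-sided .05, 96 per group, no clustering:

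| c | Diluted d | Power |
|---|---|---|
| 0 | .50 | 93.1% |
| 10% | .45 | 87.3% |
| 20% | .40 | 78.7% |
| 30% | .35 | 67.5% |

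The smallest d detectable with 80% power at 96 per group is .406, so power falls below the planned .80 once c exceeds 1 − .406/.5 = 19%.

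**The case against.** The strongest reply is that Study design already says the control group has no training in the programme, which on a plain reading rules out trained staff. The operational screen could then sit in the full protocol or the preregistration. Part of this stands: a reader who looks only at the recruitment sentence might infer that the plan knowingly admits previously trained schools, and the Study design label does not support that. But the label is undated and applies to the group, while the recruitment sentence is looser and set at school level. The article also gives the recruitment route, the matching factors, the draw and the background variables without any step that would enforce the label. The two sentences need to be aligned.

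A second reply is that the planned mixed models use a T1 measurement, so a control trained long ago with a lasting effect is raised at every wave and shows no extra change. This is right. A reader might infer that earlier training weakens T3 and T4 most; it does not, because a stable earlier effect acts equally at all waves. However, section 2.7 also plans group comparisons at each timepoint and baseline t-tests, and these are affected.

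Third, a reader might count two full semesters, 1,120 people, as potential contamination. The first 560 are roughly the experimental intake, so that count is too high.

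Fourth, admission requires the principal to apply and be prioritised, so similar pupils do not show that a school has been or will be trained. Uninterrupted delivery since 2017 is likewise inferred from the commissioning year and the recurring intake. Both points stand and are why exposure is possible rather than shown.

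Finally, dilution of this kind works toward no difference, and the only hypothesis with a stated follow-up time (H4) is at six months. This limits the seriousness but leaves the 12-month comparison open.

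**Conclusion.** The point holds in a limited form. The label in Study design and the rule in Participants and recruitment do not match, and the article describes no means of detecting or handling trained controls. Exposure is plausible because the programme takes a new intake every semester from the kind of school used for matching, with at least one later intake likely before T4.

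The consequence depends on timing. Training during follow-up would weaken the group difference at T4 and possibly T3. Stable training before T1 would mainly affect comparisons at single timepoints and baseline comparability, with little effect on change from baseline.

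The size cannot be derived from the document. If trained controls gain the full effect, 10%, 20% or 30% exposure reduces d from .50 to .45, .40 or .35, and between-group power from 93% to 87%, 79% or 67%. This assumes 96 per group, a two-sided .05 test and no clustering. It is an illustration, not an estimate, and it does not carry over to change from baseline when training precedes T1. The change is worth making because it is cheap and the data cannot be obtained afterwards.

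**What to change.** 1. Align the recruitment rule with the Study design label. Before the draw, remove from the control pool every school on the provider's list of schools already trained or already admitted to a coming intake.
2. Ask every participant at T1 whether they have had this training, at the present or a former school, and exclude controls who have.
3. Repeat the item at T2, T3 and T4.
4. Keep controls exposed after T1 in the main analysis, and state this in advance. Add a sensitivity analysis that drops their waves after exposure.
5. Report the share of controls exposed by each wave.

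The cost is one check against records held by a provider the study already works with, one survey item per wave, and a somewhat smaller pool of matched control schools.
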